## Methods

2

### Study design

2.1

This randomized placebo-controlled parallel-designed clinical trial is registered with the Australian New Zealand Clinical Trials Registry (ANZCTR), the mandated online register of clinical trials being undertaken in Australia, New Zealand, and other Oceanic Nations (Reg. No: ACTRN12623000854639).

#### Recruitment and screening

2.1.1

Advertisements will be disseminated to local community mental health teams, general practitioners, general hospitals, and other health facilities. Advertisement is also broadcast via social media networks and press launches from Townville University Hospital and James Cook University. Prospective participants register via the trial website^1^ and will then receive an email with information material relating to the structure and requirements of the trial. Prospective participants will then be screened for eligibility via telephone by the principal investigator, who is a senior psychiatrist. During the screening call or Timepoint 0 [T0], the principal investigator (CL) will check the prospective participant’s eligibility to enroll in the trial against the inclusion and exclusion criteria (Table 1).

**Table 1 tab1:** Participant eligibility.

Inclusion criteria	Exclusion criteria
To be eligible for this study, an individual must meet the following criteria: Have been diagnosed by a psychiatrist with either schizophrenia, schizoaffective disorder, or Bipolar Affective Disorder and have had the condition for at least 6 months. Being clinically stable (no episodes of hospitalization or significant treatment changes for at least 3 months) Possess the mental capacity to provide informed consent and willingness to sign a written informed consent document. Aged ≥18 years old. Able to understand the basic principles of the specific diet and follow dietary instructions as provided by the study dietitian. Willingness to adhere to all study procedures including the completion of an accurate diet and symptoms diary, daily blood glucose and ketone monitoring, and to attend the visits as scheduled.	Individuals who meet any of the following criteria will be excluded from participation in this study: Pregnant, breastfeeding, or planning to become pregnant within 3 months. Active substance misuse with alcohol or illicit drugs. Use of the ketogenic diet in the previous 2 months. Currently following a vegan diet. Admission to a mental health hospital within the past 3 months. Inability to complete visits and assessments. Uncompensated cardiovascular disease. Severe hyperlipidemia. Type 1 diabetes. History of eating disorder. BMI < 18.5 kg. On medication that can cause ketosis. Not willing to change diet or unable to change diet due to medical reasons. Active liver or kidney disease. No access to cooking facilities and ingredients to prepare recipes following the specific diet. Current involvement in another research study.

#### Assessments

2.1.2

Eligible participants progress to the first physical visit (Enrolment Visit at Timepoint 1 [T1]) and are asked to complete a three-day food diary before attending the appointment. During the enrolment visit [T1], formal written consent is obtained by a trial psychiatrist (CL, SG, or OS) before baseline assessments of psychiatric, cognitive, and metabolic outcome measures are taken. Participants are then randomized into either the Ketogenic Diet (KD) or the Australian Guide to Healthy Eating (AGHE) group by stratified, computer-generated blinded allocation. Following randomization, participants progress to the dietitian assessment and group-specific dietary education. Dietary education and counseling for each group are provided by a senior dietitian, including the provision of the existing evidence base for nutrition in mental health to assist in personalizing the KD or AGHE diet. Consideration will be given to their metabolic health, dietary preferences, age, sex, and physical activity level that may impact their estimated energy requirements (EER). Participants will then receive detailed dietary instructions and specific educational material to foster independent meal preparation. All participants, irrespective of their group allocation, will be instructed to complete a 2-week diet “adaptation period” where both groups progressively adjust their diet to minimize any side effects due to metabolic adaptation to the new diet and to allow participants to adjust their daily routine to the new food preparation requirements. Participants will be asked to complete daily food diaries and are provided with weekly dietetic support in the form of face-to-face consultation, and phone-, and email follow-up to increase compliance, alter individual diet prescriptions where required, and for safe cessation of the diet. In the second visit (Mid-Point Visit or Timepoint 2 [T2]), psychiatric and metabolic assessments are repeated. In the third visit (Completion Assessment or Timepoint 3 [T3]), all psychiatric, metabolic, and cognitive assessments are repeated. T1 is at baseline (week 0), T2 occurs on week 8, and T3 on week 14. The intervention is 12 weeks from week 3 to week 14, plus a 2-week washout period, for a total of 14 weeks duration (Figure 1). During the washout period, participants are instructed to progressively revert to a diet of their preference. Participants may also continue with their allocated diet, if they choose to do so.

Pre-existing psychiatric and metabolic treatment will continue as per the treating team’s medical advice. Metabolic medication might be adjusted for those in the KD group in collaboration with their physician to minimize the risk of hypoglycemia. Participants in both groups will be given a blood ketone and glucose monitoring device at the end of the enrolment visit (T1) and instructed to take a daily capillary blood sample to measure glucose and ketone levels. The measurement will occur consistently every day, 2 h before their routine dinner time. Daily glucose and ketone measurements are uploaded to a team’s database daily and strictly monitored to detect any emergent metabolic abnormality.

#### Allocation

2.1.3

Participants will be blinded to the study hypothesis and interact with clinicians who are kept blind to their group allocation as far as possible. Allocation will occur only after the initial psychiatrist assessment. If a psychiatrist becomes accidentally unblinded to a participant’s allocation during the running of the trial, a different team psychiatrist will be asked to continue the remaining time points assessment(s) for that participant. Participants in both groups will be treated identically in all respects except for the intervention being tested.

The study is being conducted at a single site at the Translational Research Facility, Australian Institute of Tropical Health and Medicine, James Cook University at Townsville Campus, Queensland, Australia. Human Research Ethics Approval (HREC/2022/QTHS/85408) for this study was received by the Townsville University Hospital HREC board, responsible for the study population’s catchment area.

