### Positive and negative syndrome scale

3.1

Positive and Negative Syndrome Scale (PANSS) is among the most-validated instruments for assessing positive, negative, and general psychopathology associated with schizophrenia. The PANSS is a standardized clinical interview that rates the presence and severity of positive and negative symptoms, as well as general psychopathology for people with schizophrenia within the past week. Of the 30 items, seven are positive symptoms, seven are negative symptoms, and 16 are general psychopathology symptoms. Symptom severity for each item is rated according to which anchoring points in the 7-point scale (1 = absent; 7 = extreme) best describe the presentation of the symptom (52). Positive and negative scales showed good inter-rater reliability and interclass correlation coefficients (ICC) of 0.72 and 0.80, respectively. Inter-rater reliability was moderate for the general psychopathology scale; ICC = 0.56 (53).

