
Our trial design has some limitations. Firstly, despite our best efforts to keep the overseeing psychiatrists blind to the dietary arm allocation of individual participants, we cannot rule out the possibility that some participants may disclose their diets during the psychiatric assessments in the middle or at the end of the trial. Also, an argument can be made that some of our motivated participants may have information about the expected benefits of the ketogenic metabolic therapy in their condition, which could conceivably introduce an expectation bias if assigned to the ketogenic arm of the trial. We will, however, obtain their daily blood ketone levels which can be correlated with the results of the psychiatric and cognitive assessment, and give an objective control measure to address the above limitations. Another possible limitation is that due to the nature of this clinical trial conducted in an outpatient setting, relying on the ability of the participant to adhere to a relatively restrictive dietary regime independently, the recruited participants will be better functioning than some other patients with serious mental illness, resulting in a self-selected study population. We acknowledge this limitation, but we argue that although we might be able to demonstrate better adherence in this self-selected group, it may be a strength of the trial to demonstrate symptom improvement in participants who may be somewhat better functioning already. Additionally, demonstrating adherence to a restrictive dietary regimen by a population with severe mental disorders in the community may in itself be regarded as a satisfactory outcome measure.

In conclusion, we expect this randomized controlled clinical trial to assess the feasibility, efficacy, and safety of ketogenic metabolic therapy in schizophrenia and bipolar disorder. To our knowledge, our proposed trial is the first of its kind worldwide. We hypothesize that this study will reveal improvements in symptoms, overall quality of life, and better metabolic functioning for our participants. Results from this trial may inform future studies on more specific mechanisms of action, as well as introduce a novel treatment modality to manage psychiatric disorders that would otherwise have been considered as long-term, debilitating conditions.

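### The rule for an unblinded psychiatrist covers only later time points, so a diet disclosed during the T2 or T3 interview leaves that visit's PANSS and YMRS ratings unblinded

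*Protocol article*

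**What the plan says.** All of this comes from the protocol article.

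- **The rule (2.1.3 Allocation).** The trigger is broad: "If a psychiatrist becomes accidentally unblinded to a participant’s allocation during the running of the trial". The action is narrower: "a different team psychiatrist will be asked to continue the remaining time points assessment(s) for that participant".
- **Baseline (2.1.3).** "Allocation will occur only after the initial psychiatrist assessment", so the T1 rating is made before there is an allocation to disclose.
- **Visits (2.1.2 Assessments).** "T1 is at baseline (week 0), T2 occurs on week 8, and T3 on week 14". At the mid-point: "In the second visit (Mid-Point Visit or Timepoint 2 [T2]), psychiatric and metabolic assessments are repeated". At the end: "In the third visit (Completion Assessment or Timepoint 3 [T3]), all psychiatric, metabolic, and cognitive assessments are repeated". No later assessment is planned.
- **Acknowledged route of unblinding (9 Discussion).** As a limitation, the authors say they cannot rule out that "some participants may disclose their diets during the psychiatric assessments in the middle or at the end of the trial". In the same paragraph they offer the daily ketone readings, correlated with the psychiatric and cognitive results, as an objective control.
- **Scales affected.** The abstract lists six primary measures. PANSS (3.1) and YMRS (3.2) are scored by a clinician at interview. BDI and WHODAS 2.0 are reported by the patient, the ALS-18 is likewise a questionnaire, and CANTAB is delivered on a tablet.

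**The concern.** Participants know which diet they follow, and the Discussion grants that some may hold expectations about the ketogenic diet. For PANSS and YMRS, the main protection against such expectations reaching the score is a psychiatrist who does not know the arm.

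The stated safeguard works when the blind breaks between visits: the next rating goes to someone else. The Discussion names a different route, in which the participant mentions the diet during the interview being scored. As worded, the rule does not reach that rating. The psychiatrist who has just learned the arm goes on to score two primary scales, and at T3 no later blinded rating exists to set beside that score.

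**Working it through.** **1. The rule set against the visit schedule.** This part needs only the text of 2.1.2 and 2.1.3.

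| When the psychiatrist learns the arm | Time points remaining | Rating left unblinded | Rating protected by the rule |
|---|---|---|---|
| At T1 | not applicable (allocation comes later) | none | not applicable |
| Between T1 and T2 | T2, T3 | none | T2, T3 |
| During the T2 interview, before scoring ends | T3 | T2 | T3 |
| Between T2 and T3 | T3 | none | T3 |
| During the T3 interview, before scoring ends | none | T3 | none |
| After T3 scoring is complete | none | none | none needed |

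The two rows with an unblinded rating are the two situations named in the Discussion.

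**2. Whether the ketone correlation repairs this.** The diet is designed to raise ketones in one arm, so across both arms the ketone level largely stands in for the allocation. A true diet effect would produce an association between ketones and ratings. So would a psychiatrist who scores known ketogenic participants more favourably. The correlation also does not show which ratings were made with knowledge of the arm. It cannot tell the two explanations apart.

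**3. The plan's own sample size, used below.** Section 8.1 assumes 75% against 40% improved, two-sided 5% significance and 90% power. The pooled proportion is 0.575.

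n per arm = [1.960 × √(2 × 0.575 × 0.425) + 1.282 × √(0.75 × 0.25 + 0.40 × 0.60)]² / 0.35² = (1.370 + 0.838)² / 0.1225 ≈ 39.8, so 40.

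That gives 80 in total, and 80 / 0.80 = 100 to recruit. The stated figures reproduce and are not in dispute.

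**4. Illustration of size.** The documents give no disclosure rate and no rater shift, so both inputs are assumptions. Let f be the fraction of T3 ratings unblinded in one arm (none in the other) and b the shift in SD of an unblinded score.

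Bias in the arm difference = f × b.

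- Low end: 0.10 × 0.3 = 0.03 SD.
- High end: 0.50 × 0.5 = 0.25 SD.

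With 40 per arm, unit SD, no true effect and a simple T3 comparison, SE = √(2/40) = 0.224. The two-sided type I error is Φ(fb/SE − 1.96) + Φ(−fb/SE − 1.96).

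- fb = 0.03: fb/SE = 0.13, type I error about 0.05.
- fb = 0.10 (f = 0.25, b = 0.4): about 0.073.
- fb = 0.20 (f = 0.50, b = 0.4): about 0.146.
- fb = 0.25: fb/SE = 1.12, about 0.20.

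If disclosure is rare the effect is negligible. If it is common and one-sided it is not. Disclosure in both arms with shifts in the same direction would partly cancel.

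**The case against.** **The authors already admit it.** They do, and they deserve credit for it. But they say only that disclosure cannot be ruled out. A reader might infer that they expect it, and the text does not go that far. The admission also leaves the rule unchanged.

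**A condensed article leaves such detail to the full protocol or the SAP.** This is fair for rater logs, flags and sensitivity analyses; their absence here is not the finding. The finding is that the one rule the article does state misses the visit at which the blind breaks. An SAP can flag an unblinded T3 rating afterwards, but it cannot make that rating blind.

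**The wording could include an unfinished visit.** A hand-over during the current visit is compatible with the text, but it is not stated. If it is intended, one sentence settles the matter.

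**Disclosure may cluster in the ketogenic arm.** A reader might infer this from the more unusual diet, or from the possible adjustment of metabolic medication in that arm (2.1.2). The documents give no disclosure rates by arm. Both arms receive meters, food diaries and weekly dietetic support, and participants are blinded to the hypothesis. Imbalance is possible but not shown, and the gap at T2 and T3 does not depend on it.

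**Changing raters may itself look harmful.** A reader might infer this from section 3.1, where "Inter-rater reliability was moderate for the general psychopathology scale; ICC = 0.56". That value is cited from the literature and is not from this trial's psychiatrists; the positive and negative scales have 0.72 and 0.80, and no value is given for YMRS. Random differences between raters cost precision but do not by themselves bias the arm comparison. A change of rater is the accepted price of a blind rating.

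**Conclusion.** The concern holds in a limited form. As written, the rule protects neither rating after a disclosure during the T3 interview, and only the T3 rating after a disclosure during T2. The ketone correlation does not make up for this. Of the six primary measures, only PANSS and YMRS are affected; for both, the rule still works when unblinding occurs between visits.

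The gap follows from the wording and the visit schedule alone. Its size does not. The range of 0.03–0.25 SD rests on assumed values of 10–50% unblinded in one arm only and a shift of 0.3–0.5 SD, and the upper end needs both upper values together. A reader might also infer that T3 alone decides the result. Section 8.2 does not say so: it plans mixed models, and the psychiatric scales are also taken at T2. The change is worth making because it costs little and a blind T3 rating cannot be recovered later.

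**What to change.** Reword the rule in 2.1.3 so that it acts at the same visit.

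1. Before T2 and T3, ask each participant not to mention their diet to the psychiatrist.
2. At those visits, complete and lock PANSS and YMRS first.
3. If diet is disclosed before the scores are locked, another of the existing trial psychiatrists completes the rating at that visit or within a few days. The present rule continues to apply to later time points.
4. For every PANSS and YMRS rating, record the rater's identity and whether the rater was unblinded (yes/no).
5. Report the unblinding counts by arm, and repeat the PANSS and YMRS comparisons without flagged ratings as a sensitivity analysis.

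The cost is one procedural paragraph, two case-report-form fields, an occasional rescheduled interview, some additional rater changes and one extra analysis. Substitute psychiatrists are already part of the plan, and the sample size does not change.

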### Experimental intervention

2.2

The intervention involves a 12-week dietitian-led, medically supervised KD, designed to induce a state of nutritional ketosis. Several dietary regimes for achieving ketosis in adults exist including the Modified Atkins Diet (MAD)/ Modified Ketogenic Diet (MKD), Low Glycaemic Index Treatment (LGIT), and the Classical Ketogenic Diet (Table 2). These diets share a common principle of reducing carbohydrate (CHO) intake while increasing fat consumption. The variation in the degree of CHO reduction and fat increase distinguishes these regimes. In this trial, a MKD (2:1 ratio) will be implemented to induce ketosis in participants. The MKD was selected for its higher compliance rates (49, 50) and its allowance for greater flexibility and food variety compared to the classical ketogenic diet (4:1 ratio). The prescribed amount of macronutrient distribution will aim for approximately 75% of EER from fat, 5% from CHO, and the remaining from protein. Additionally, participants following the MKD will be recommended to supplement with a CHO-free multivitamin in accordance with best practice guidelines (49).

**Table 2 tab2:** Most commonly used therapeutic Ketogenic diets.

	Modified Atkins diet	Modified Ketogenic diet	Low glycaemic index treatment	Classic Ketogenic diet
Fat (%)	65	75	60	90
Carbohydrates (%)	10	5	10	4
Protein (%)	25	20	30	6

### Control diet

2.3

The study’s control group adheres to a 12-week regimen of dietitian-led and medically supervised nutrition, aligning with the principles outlined in the Australian Guide to Healthy Eating (AGHE). Macronutrient intake, including carbohydrates, fat, and protein, is calculated to match individual factors such as age, weight, and level of physical activity as set out in the guidelines. Within this framework, the recommended optimal macronutrient ranges from the AGHE are encouraged, with protein comprising 11%, fats ranging from 20 to 35%, and the remainder from carbohydrates (see Table 3) (51).

**Table 3 tab3:** Ketogenic diet vs. the Australian guide to healthy eating.

Ketogenic diet	Australian guide to healthy eating
< 50 g of carbohydrates per day Total daily calories: 70–80% fat 5–10% carbohydrates 10–20% protein	Plenty of vegetables of different types and colors, and legumes/beans Fruit Grain (cereal) foods, mostly wholegrain and/or high cereal fiber varieties, such as breads, cereals, rice, pasta, noodles, polenta, couscous, oats, quinoa, and barley Lean meats and poultry, fish, eggs, tofu, nuts and seeds, and legumes/beans Milk, yogurt, cheese, and/or their alternatives, mostly reduced fat

## Psychiatric outcome measures

3

### Positive and negative syndrome scale

3.1

Positive and Negative Syndrome Scale (PANSS) is among the most-validated instruments for assessing positive, negative, and general psychopathology associated with schizophrenia. The PANSS is a standardized clinical interview that rates the presence and severity of positive and negative symptoms, as well as general psychopathology for people with schizophrenia within the past week. Of the 30 items, seven are positive symptoms, seven are negative symptoms, and 16 are general psychopathology symptoms. Symptom severity for each item is rated according to which anchoring points in the 7-point scale (1 = absent; 7 = extreme) best describe the presentation of the symptom (52). Positive and negative scales showed good inter-rater reliability and interclass correlation coefficients (ICC) of 0.72 and 0.80, respectively. Inter-rater reliability was moderate for the general psychopathology scale; ICC = 0.56 (53).

### The young mania rating scale

3.2

The Young Mania Rating Scale (YMRS) is a clinical interview scale and is one of the most frequently utilized rating scales to assess the severity of manic states in bipolar affective disorder. The scale has 11 items and is based on the patient’s subjective report of his or her clinical condition over the previous 48 h. Additional information is based on clinical observations made during the clinical interview. The items are selected based on published descriptions of the core symptoms of mania. The YMRS follows the style with each item given a severity rating. Four items are graded on a 0 to 8 scale (irritability, speech, thought content, and disruptive/aggressive behavior), while the remaining seven items are graded on a 0 to 4 scale. These four items are given twice the weight of the others to compensate for poor cooperation from severely ill patients (54).

### World health organization disability assessment schedule, version 2

3.3

The World Health Organization Disability Assessment Schedule, version 2 (WHODAS 2.0) is the standard measure of disability promoted by the World Health Organization. WHODAS 2.0 is a patient-reported outcome instrument that uses 36 questions to assess the global health status of patients across 6 health domains, i.e., Cognition, Mobility, self-care, social interaction, life activities, and social participation. The WHODAS 2.0 is a validated and established questionnaire that can be used to assess the health status of patients irrespective of disease (55).

